#### Methods in analysis to handle protocol non-adherence and any statistical methods to handle missing data {20c}

We are planning to perform an intention-to-treat analysis, and we will manage missed data by analyzing the available data or by multiple imputations—reporting the method used.

#### Plans to give access to the full protocol, participant level-data and statistical code {31c}

We seek to publish the full protocol; besides, we have uploaded the protocol on the clinical trial registry. The CRF with the statistical code is provided as a supplement (supplement S3) to the protocol.

### Oversight and monitoring

#### Composition of the coordinating center and trial steering committee {5d}

The lead investigator is responsible for trial supervision, local organization, and identifying of the potential recruits. One chest physician and a clinical pharmacist conducted the informed consent process. The trial members met periodically online to oversee conduct and progress—at least at the time of evaluation of the interim analyses. In addition, we used WhatsApp for instantaneous communications—without circulating any of the patients’ data identifiers.

#### Composition of the data monitoring committee, its role and reporting structure {21a}

We had the COVID-19 scientific committee at Mansoura University as the DSMB. The members of the board have no direct role in the study. They monitor and evaluate the study conduct, interim analyses, and adverse events.

#### Adverse event reporting and harms {22}

We planned to report any in-hospital adverse events by the study investigators or the out-of-hospital adverse events by the patients. Patients have telephone contacts with WhatsApp for reporting any adverse events or discontinuation of the study drug. We did not receive any serious adverse events to report to the IRB or the DSMB.

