### Criteria for discontinuing or modifying allocated interventions {11b}

The safety assessment included daily monitoring for adverse events; we checked CK level if the patient developed myalgia or unexplained weakness and stopped if CK > 10 times ULN, drug-induced hepatitis, or serum transaminases > 8 times ULN. Patients who received azole antifungals had a lower threshold for monitoring of liver injury and rhabdomyolysis.

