### Sample size {14}

A sample size of 97 patients in each group would achieve at least 80 % power to detect a risk difference of 0.2 (20%) in the 28-day all-cause mortality (primary outcome) between the null hypothesis (both proportions are 0.6) and the alternative hypothesis (the proportion in the non-statin group would be 0.4).

Based on two large studies on chronic use of statin in hospitalized COVID patients, the adjusted OR of mortality was 0.52 and 0.67, which corresponds to a risk reduction of 17–27 % in mortality when the mortality is 60% in the control group; therefore, we used the 20% reduction in our assumption of the sample size [21, 22].

We assumed a significance level (*α*) of 0.05 and used the chi-square test of independent proportions in MedCalc software.

To compensate for the estimated loss-to-follow-up, we increased the sample size to be 110 patients in each group.

The mortality in the control group (60%) was estimated from the average mortality in January, February, and March 2021 at the Mansoura University Isolation Hospital among all hospitalized patients.

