#### Interim analyses {21b}

After recruitment of 25, 50, and 75% of the planned sample size, we performed interim analyses of the in-hospital mortality.

The Data Safety Monitoring Board (DSMB) and the IRB members were blinded for the study allocation. Results of the interim analysis are presented in Fig. 2. They were timely reported and revised by the IRB and the DSMB.

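### The report that no serious adverse events were received depends on an unstated counting rule, and the one outcome worded as an adverse effect omits unlisted serious events that did not stop the drug

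*Protocol article*

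**What the plan says.** Adverse event reporting and harms {22} sets out a plan to report any adverse event, from investigators in hospital and from patients after discharge. It then gives a result: "We did not receive any serious adverse events to report to the IRB or the DSMB".

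Other sections of the protocol article bear on that sentence:

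- **Inclusion criteria:** only adults with severe or critical COVID-19 were enrolled.
- **Sample size {14}:** the trial was planned on mortality of 60% v 40%, with 110 patients per group after allowance for loss. "The mortality in the control group (60%) was estimated from the average mortality in January, February, and March 2021".
- **Interim analyses {21b}:** in-hospital mortality was analysed after 25%, 50% and 75% of recruitment. "Results of the interim analysis are presented in Fig. 2. They were timely reported and revised by the IRB and the DSMB". The section on communicating amendments {25} repeats that these results went to both bodies.
- **Secondary outcomes:** one item is worded as an adverse effect, and it is limited to serious effects that led to stopping the study drug. Invasive ventilation, acute kidney injury (AKI), in-hospital deep vein thrombosis (DVT) or pulmonary embolism (PE), and mortality at discharge are listed separately without that condition. All-cause death within 28 days is the primary outcome.
- **Criteria for discontinuing {11b}:** adverse events were monitored daily, but for creatine kinase "we checked CK level if the patient developed myalgia or unexplained weakness".

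**The concern.** Death is ordinarily a serious adverse event. In a trial of this population and planned mortality, a report of none received must rest on some restriction in what was counted, and the article does not say what it was. A reader of the results could take the zero for a clean safety profile when it may only reflect how events were classified.

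The listed outcome does not fill the gap. A serious liver or muscle event in a patient who stayed on the study drug belongs to no listed outcome. Yet CK and transaminases are the laboratory signals that the protocol uses for both exclusion and stopping. For CK, few abnormal results could also reflect few tests.

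**Working it through.** **1. The plan's own figure.** Inputs from Sample size {14}: p1 = 0.60, p2 = 0.40, alpha 0.05 (taken as two-sided, since the side is not stated), power 80%, chi-square test.

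n = [1.960 × √(2 × 0.5 × 0.5) + 0.8416 × √(0.6 × 0.4 + 0.4 × 0.6)]² / 0.2²

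= [1.3859 + 0.5831]² / 0.04 = 3.877 / 0.04 = 96.9, so 97 per group, with power 0.800 at that size. This agrees with the plan: "A sample size of 97 patients in each group would achieve at least 80 % power". The mortality rates below are therefore the ones on which the trial was sized. The section attaches the 0.4 to the non-statin group, against the study hypothesis, but this changes neither n nor the total deaths below.

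**2. Deaths expected among the 220 patients (110 per arm).** Expected deaths = 110 × p1 + 110 × p2.

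| Scenario | Expected deaths |
|---|---|
| 60% v 40% (design alternative) | 66 + 44 = 110 |
| 60% in both arms | 132 |
| 40% in both arms | 88 |

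**3. Could there have been no deaths?** The chance is (1 − p)^220.

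- At p = 0.40: 0.60^220 ≈ 1.6 × 10⁻⁴⁹.
- At an assumed p = 0.05, far below the planning rates: 0.95^220 ≈ 1.3 × 10⁻⁵.

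The conclusion does not depend on the planned 60% being accurate.

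**4. What the interim analyses would have shown.** The looks fall at 0.25, 0.50 and 0.75 × 220 = 55, 110 and 165 patients. At 50% average mortality that is about 28, 55 and 83 deaths, before allowing for incomplete follow-up and for the interim measure being in-hospital death. The observed counts are in Fig. 2, which is not available here.

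**5. Which events reach a listed between-arm outcome.**

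| Event | Listed outcome? | Needs the drug to be stopped? |
|---|---|---|
| Death | Yes (primary and secondary) | No |
| Invasive ventilation | Yes | No |
| AKI, DVT or PE | Yes, in hospital | No |
| Serious hepatic or muscle event | Only through the adverse-effect item | Yes |
| Other serious event not listed | Only through the adverse-effect item | Yes |

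The exclusion limits are 5 times the upper limit of normal (ULN) for both CK and transaminases. The stopping limits are 10 times for CK and 8 times for transaminases. A rise past the first limit but not the second would not by itself meet the laboratory stopping limit, so it need not appear in the adverse-effect item.

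**The case against.** The strongest reply is that the sentence concerns events received for reporting, not events that happened. A reader might infer that the protocol claims nobody died or had a serious event. The documents do not support that: mortality went to the IRB and DSMB through the interim analyses, so deaths were not hidden from them. This part of the reply stands, and the expected 110 deaths should not be set against a claimed count of zero deaths. They show only that a restriction on what counted must have been in force.

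A reader might also infer that harm is understated by construction, or that fatal and renal harm go uncompared. That fails too. Every death within 28 days enters the primary comparison whatever its cause. In-hospital AKI, DVT or PE, and ventilation are outcomes regardless of discontinuation. Adverse events were monitored daily, with a plan to report any of them.

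Nor can the zero be taken to mean that none was judged drug-related. An exemption for events already captured as trial outcomes fits equally well, and the article does not decide between the two.

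Finally, the full protocol or the case report form may define a serious event, so the missing definition is not in itself an error. This is right, but it does not excuse an unqualified zero in the article that conflicts with the article's own mortality figures.

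On CK, the trigger includes weakness as well as myalgia, and weakness can be found on examination. So the limitation for ventilated or unconscious patients is partial, not complete.

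**Conclusion.** The point holds in two limited parts.

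First, the sentence on serious adverse events cannot be read literally beside the inclusion criteria, the sample size and the interim analyses. It needs the rule that makes it true. The planning figures imply 88 to 132 deaths, and even at 5% mortality the chance of none is about 1 in 80,000 (1 / 1.26 × 10⁻⁵). These are expectations, not observed counts. The 60% came from all patients hospitalised in early 2021, whereas the trial excluded those expected to die within 48 hours. The conclusion also assumes that deaths would ordinarily count as serious.

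Second, serious hepatic, muscle or other unlisted events without discontinuation lie outside the listed outcomes. The number of such events cannot be estimated from the article. Treatment comparisons of death, ventilation, AKI and DVT or PE are unaffected. This is worth correcting before results are reported, but it is no evidence that harm occurred or was concealed.

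**What to change.** 1. **State the rule.** Reconcile Adverse event reporting and harms {22} with Sample size {14}, Interim analyses {21b} and the section on communicating amendments {25}. Say which events counted as serious and whether deaths and other trial outcomes were exempt. Use the rule that was actually applied, without presuming that it was attribution to the drug.
2. **Widen the outcome.** Replace the discontinuation-based item under Secondary outcomes with a by-arm count of all recorded serious adverse events, regardless of attribution or discontinuation. Keep those that led to stopping as a subset, so that nothing now planned is lost. As recruitment has ended, mark this as a change made after it.
3. **Give the laboratory denominators.** Where existing records allow, report by arm the counts above the protocol's own CK and transaminase limits, with the number of patients tested as denominator.

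No change to clinical monitoring or to the stopping rules is proposed. The cost is a clarified sentence and one extra safety table, with no new visits or tests. The laboratory counts will describe only the patients who were tested, and should say so. What the case report form captured is not shown, so item 3 may be possible only in part.

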#### Frequency and plans for auditing trial conduct {23}

We met at least for 3 times during the conduct of the study to view the interim analyses and to review the trial conduct. We contacted the IRB and the DSMB at each interim analysis stage to report the study progress.

#### Plans for communicating important protocol amendments to relevant parties (e.g., trial participants, ethical committees) {25}

We reported the interim analyses results to the IRB and the DSMB. Additionally, we reported the end of the patients’ recruitment to the IRB, DSMB, and updated the study status on the Clinical Trial registry.

#### Dissemination plans {31a}

We would report our results in a preprint server while aiming for publication in peer-review journals. We will report the early study outcomes, then the late 6-month outcomes in a separate later-on publication.

## Discussion

The additional issue that we would like to discuss is the added workload on the clinicians and the allied healthcare workers who performed research at the time of the pandemic. Therefore, doing research at the pandemic era was, indeed, challenging. At the beginning, the stakeholders did not give the researchers the needed space, however, we had some support at Mansoura University, and we could involve the COVID scientific committee to support the study.

## Trial status

This is the third version of the protocol approved by the IRB at Mansoura University, Faculty of Medicine. We started the study recruitment on August 18, 2021, and the patients’ recruitment end on October 6, 2021. Currently, we are collecting data for the long-term follow-up. Due to the pandemic workload, the investigators could not submit the protocol for publication at earlier stage.

## Data Availability

We will make the anonymous individual data available at reasonable request after publication. Patient confidentiality will be kept.

## Abbreviations

AF: Atrial fibrillation
AKI: Acute kidney injury
ARDS: Acute respiratory distress syndrome
CARDS: COVID-19 ARDS
CK: Creatine kinase
COPD: Chronic obstructive pulmonary disease
COVID-19: Coronavirus disease of 2019
CRF: Case report form
DM: Diabetes mellitus
DSMB: Data and Safety Monitoring Board
HMG-CoA: β-Hydroxy β-methylglutaryl-CoA
HTN: Hypertension
ICU: Intensive care unit
IHD: Ischemic heart disease
IL-6: Interleukin-6
IRB: Institutional research board
NF-κB: Nuclear factor kappa B
NLRP3: Nod-like receptor pyrin domain containing 3
PAI-1: Plasminogen activator inhibitor-1
PCR: Polymerase chain reaction
PE: Pulmonary embolism
PFTs: Pulmonary function tests
RR: Respiratory rate
SARS: Sever acute respiratory syndrome
SARS-COV-2: Severe acute respiratory syndrome - coronavirus 2
SOFA score: Sequential organ failure assessment
